## Abstract

**Background:**

Weil osteotomies are performed to surgically treat metatarsalgia, by shortening the metatarsal via either a single distal oblique cut with translation of the metatarsal head (flat-cut) or through the removal of a slice of bone (wedge-cut). The wedge-cut technique purportedly has functional and mechanical advantages over the flat-cut procedure; however, in vivo data and quality of evidence are currently lacking. This study aims to investigate whether wedge-cut Weil osteotomy compared to traditional flat-cut Weil is associated with increased pain relief and fewer complications up to 12 months postoperatively.

**Methods:**

Patient, surgical and clinical data will be collected for 80 consecutive consenting patients electing to undergo surgical treatment of propulsive metatarsalgia in a randomised control trial, embedded within a clinical registry. The primary outcome is patient-reported pain as assessed by the Foot and Ankle Outcome Score (FAOS) - Pain subscale, and the secondary outcome is the incidence of procedure-specific complications at up to 12 months postoperatively. The groups will be randomised using a central computer-based simple randomisation system, with a 1:1 allocation without blocking and allocation concealment. A mixed-effects analysis of covariance will be used to assess the primary outcome, with confounders factored into the model. A binary logistic regression will be used to assess the secondary outcome in a multivariable model containing the same confounders.

**Discussion:**

To the best of the authors’ knowledge, the trial will be the first to examine the clinical efficacy of the wedge-cut Weil osteotomy compared to the flat-cut technique with a prospective, randomised control design.

**Trial registration:**

Australian New Zealand Clinical Trials Registry ACTRN12620001251910. Registered on 23 November 2020.

**Supplementary Information:**

The online version contains supplementary material available at 10.1186/s13063-022-06591-4.

## Administrative information

Note: The numbers in curly brackets in this protocol refer to SPIRIT checklist item numbers. The order of the items has been modified to group similar items (see http://www.equator-network.org/reporting-guidelines/spirit-2013-statement-defining-standard-protocol-items-for-clinical-trials/).

## Introduction

### Background and rationale {6a}

Propulsive metatarsalgia is defined as pain under one or more metatarsal heads during the “third rocker” phase (30 to 60%) of the gait cycle, from heel lift-off to the end of propulsion by the great toe [1]. Weil osteotomy is a reliable distal oblique osteotomy procedure performed to treat lesser metatarsal deformities and alleviate metatarsalgia, by shortening the metatarsal in the transverse plane. The osteotomy is performed with or without adjunct procedures for toe correction, which may include proximal interphalangeal arthrodesis [2], fusion/arthrodesis of the first metatarsophalangeal (MTP) joint [3] or hallux valgus correction [4]. While Weil osteotomies are commonly performed, complications include floating toe, joint stiffness, avascular necrosis, transfer of metatarsalgia to subsequent toes and plantar flexion of the metatarsal [1, 5, 6].

Traditional flat-cut Weil osteotomies involve a single distal oblique incision in the dorsal aspect of the metatarsal head, with translation of the head by 5–10 mm. Wedge-cut osteotomy is a modification of the flat-cut Weil procedure and includes a second incision to remove a slice of bone [1]. A wedge is created either with parallel sides or with an apex on the plantar aspect of the metatarsal, and the procedure is purported to reduce plantar translation of the metatarsal head, maintain the MTP centre of rotation and improve intrinsic muscle function as demonstrated on sawbone models [7]. However, there is limited in vivo data for the clinical efficacy of this technique, and the quality of evidence is lacking [7, 8].

The proposed study has therefore been designed to investigate whether the modified wedge-cut Weil osteotomy compared to the flat-cut technique, with or without required adjunct procedures, is associated with increased pain relief and fewer complications at up to 12 months postoperatively in patients presenting with propulsive metatarsalgia.

### Objectives {7}

The primary objective of this study is to determine, in patients electing to undergo surgical intervention for propulsive metatarsalgia, whether wedge-cut osteotomy compared to flat-cut Weil (with or without adjunct procedures) is associated with increased pain relief during activities of daily living up to 12 months postoperatively. The secondary objective of this study is to determine whether a lower incidence of procedure-specific complications (floating toe or stiffness) at up to 12 months of follow-up is associated with the wedge-cut procedure, compared to the flat-cut Weil.

### Trial design {8}

The proposed study is designed as a randomised controlled superiority trial with two parallel groups comprising 1:1 allocation.

## Methods: participants, interventions and outcomes

### Study setting {9}

Patient recruitment and data collection will be performed at the private hospitals and consulting clinics for the participating surgeons (New South Wales, Australia). Recruitment is expected to be complete by April 2023. Patients will be randomly allocated to either intervention using a central computer-based allocation randomisation system prior to surgery. The trial is embedded in a clinical registry with patient, surgical and clinical data captured as part of routine clinical care. Figure 1 outlines the schedule of study activities, and Fig. 2 outlines the study design for the trial described above.

**Fig. 1 Fig1:**
[figure not shown]
Schedule of enrollment, interventions and assessment for the trial

**Fig. 2 Fig2:**
[figure not shown]
Study design for the randomised control trial

The trial is scheduled to commence in January 2021 and is due to be completed by June 2023. The study has been registered on an online registry for clinical trials (Australia New Zealand Clinical Trial Registry (ANZCTR)), where the study site and sponsor details are listed (ACTRN12620001251910). The study will be reported as per the CONSORT guidelines [7, 8].

### Eligibility criteria {10}

Patients presenting to the participating surgeons for treatment of propulsive metatarsalgia who are over 18 years of age and eligible for surgical intervention (having failed a minimum of six months of conservative interventions) will be eligible for recruitment. Patients will need to be registered in the SOFARI registry and provide additional written informed consent for participation in the present randomised controlled trial.

Patients who have declined or revoked consent for use of clinical data for research (for the SOFARI registry or the current trial) or are unable to provide informed consent will be excluded. Patients will additionally be excluded if they have had recent (< 6 months) prior surgery to the affected forefoot, if they require additional procedures involving the soft tissues of the foot-ankle complex, have had their surgery booking cancelled with the participating surgeon or have been judged by the participating surgeons as incapable to complete patient reported outcome measures (PROMs) as required for the study due to psychological impairment or insufficient English language capacity (Fig. 3).

**Fig. 3 Fig3:**
[figure not shown]
CONSORT diagram [7] with the key stages identifying patients that will be included in the analysis. *R* indicates randomisation

### Who will take informed consent? {26a}

The participating surgeons will discuss the study with prospective participants and obtain written informed consent prior to the participant undergoing surgery.

### Additional consent provisions for collection and use of participant data and biological specimens {26b}

Potential uses of the datasets generated and/or analysed during the trial may include subsequent analysis of subgroups for investigation of surgical/management and patient-centred outcomes for internal clinic purposes.

The research data may form the basis of potential future studies, including additional research sites within allied health networks or collaborations with other research groups for the biomechanical evaluation of patients. Where appropriate, open-access principles will be followed to enable collaborative works with aligned groups, where the interest is academic and not for commercial uses, under appropriate licencing arrangements of de-identified data. Any future studies requesting the use of this data will seek appropriate amendment of the relevant ethical approval, and further consent will be obtained or waived on application to the HREC, as appropriate.

### Interventions

#### Explanation for the choice of comparators {6b}

The two interventions are used by the participating surgeons for the surgical management of metatarsalgia.

#### Intervention description {11a}

Eligible patients will be randomised in equal proportions between those receiving the flat-cut Weil osteotomy (the “control” intervention, group A) and the wedge-cut Weil osteotomy (the “experimental” intervention, group B).

Group A will receive an active control intervention. Preoperative planning will be undertaken to determine the amount of metatarsal shortening required to restore the parabola of the affected metatarsal. The amount of shortening will be determined by recreating the Maestro criteria for metatarsal parabola [9]. At the time of surgery, the patient will be prepared in the standard fashion, placed supine on the operating table with the operated limb prepared and draped to create a sterile area. General intravenous sedation will be administered in addition to prophylactic antibiotics, and an ipsilateral ankle tourniquet is applied and inflated prior to the first incision. A semi-elliptical transverse incision will be used to expose each metatarsophalangeal joint to be operated, spanning between the tendons of the extensor muscles without cutting or lengthening the tendons. Additional care will be taken to avoid release of other soft tissues such as the medial and lateral collateral ligaments.

The metatarsal and phalangeal joint surfaces will be inspected and additional resection performed to remove plantar capsule adhesions where required [10]. The metatarsal bone will be dissected, retracting other soft tissues, including the joint capsule to aid in visualisation and access to the metatarsal neck. A rasp will be used to remove the soft tissue on either side of the osteotomy location. The dorsal zone of cartilage inferior to the metatarsal head will be identified and used as a landmark for the osteotomy. Neurovascular bundles in the intertarsal space will be retracted and a microsagittal motorised saw held parallel to the weight-bearing surface of the foot moved from the dorsal to plantar cortices of the metatarsal to dissect the head from the neck in preparation for repositioning. The plantar plate will be inspected and repaired as required and the metatarsal head shifted proximally to achieve the desired shortening, avoiding medial or lateral shifting.

The osteotomy will be stabilised with a Kirschner wire placed across the osteotomy (along the metatarsal shaft) to guide screw fixation. Once the screw is fully engaged, the K-wire will be removed. The overhanging bone ledge will be resected with a bone saw or rasp, followed by releasing of the soft tissues under retraction closure of the joint capsule. The remaining soft tissues will be closed in layers and dressed with strips and bandages. The patient will be moved to recovery and discharged as per normal.

The preparation of the patient and surgery site for group B will be as described for group A (the control intervention). The surgical procedure will be modified by adding a second osteotomy proximally to remove a rectangular wedge of bone for the purposes of shortening the metatarsal and repositioning the floating segment of the metatarsal head proximally to the metatarsal neck [11].

Postoperative management for both groups will include elevation of the foot for the initial 72 h after surgery and stitches removed in 10–14 days. Analgesics and antibiotics will be prescribed for the first 14 days after surgery, with weight bearing as tolerated.

#### Criteria for discontinuing or modifying allocated interventions {11b}

If the participant requests a particular intervention, they will be unenrolled from the trial, and their data will not be included in later analyses.

#### Strategies to improve adherence to interventions {11c}

Adherence to the randomised intervention allocation will be assessed by comparing the patient osteotomy group allocation as identified in the operation report, to the trial master sheet with the allocation information. Follow-up and PROM compliance will be encouraged through follow-up reminders, as part of the SOFARI registry processes. The primary outcome will be collected electronically, with controls in place to prevent partial completion of the questionnaire.

#### Relevant concomitant care permitted or prohibited during the trial {11d}

If required, the osteotomies (both control and interventional) are performed with adjunct procedures for toe correction, based on the individual case and patient’s anatomy:Proximal interphalangeal arthrodesis, which involves the longitudinal insertion of a Kischner wire or pin to fuse the most proximal joint of the lesser toe [2]Fusion/arthrodesis of the first MTP joint, which involves the longitudinal insertion of a Kirschner wire or pin to fuse the most proximal joint of the first ray [3]Hallux valgus correction, which is a correcting osteotomy performed to realign the first ray in the presence of first tarsometatarsal joint hypermobility [4]

No specific postoperative prohibitions above the standard of care will be communicated to participants during the trial.

#### Provisions for post-trial care {30}

Patients enrolled in the study are covered by indemnity for negligent harm through standard medical indemnity insurance. The intervention is routine and well-practised, and the insurance covers non-negligent harm associated with the protocol. This includes cover for additional health care and compensation or damages, whether awarded voluntarily or by claims pursued through the courts. Incidences judged to arise from negligence (including those due to major protocol violations) will not be covered by study insurance policies.

### Outcomes {12}

#### Primary outcome measures

The primary outcome of this trial will be the Foot and Ankle Outcome Score (FAOS) - Pain subscale, collected at up to 12 monthly postoperatively. The FAOS was developed as a foot and ankle-specific PROM assessment analogous to the Knee injury and Osteoarthritis Outcome Score (KOOS), with content validity confirmed with 213 patients with ankle instability [12]. The FAOS consists of 5 subscales: pain, other symptoms, function in daily living (ADL), function in sport and recreation (Sport(Rec)), and foot- and ankle-related quality of life (QOL). Patients rate the questions on a 5-point Likert scale, with 0 representing no symptoms/problems and 4 representing extreme symptoms. The FAOS has been used in patients with lateral ankle instability, Achilles tendonitis and plantar fasciitis, with reliability confirmed in instability patients [12] and responsiveness confirmed in patients with Achilles tendinosis [13] and hallux rigidus [14]. Given the interventions performed in this trial are to treat metatarsalgia, a condition characterised by pain during weight-bearing activity, particularly noticeable during the push-off phase of the gait cycle, the pain subscale of the FAOS Questionnaire was selected as the most clinically relevant patient-reported measure for the purposes of measuring the primary outcome of this trial. One study reported an MCID of 15.3 points (95% confidence interval 10–20.6) [15], with a difference between groups equal to half this (7.7) deemed sufficient to guide future decision-making with respect to technique selection. For analysis purposes, a mixed-effects model will be used, which will aggregate scores from all responders and report mean and standard deviation (SD) associated with different combinations of model predictors, such as intervention group, sex and adjunct procedures.

#### Secondary outcome measures

The secondary outcome of this trial will be the incidence of procedure-specific complications at up to 12 months postoperatively. The most commonly reported complication of the Weil osteotomy is a floating toe, with an overall occurrence of 36% [6]. A floating toe is defined as a toe that is not in contact with the floor under weight-bearing conditions [16]. It will be recorded using a weight-bearing coronal view static photograph and manually rated. Recurrence is reported in 15% of the cases, followed by transfer metatarsalgia (7%) and delayed union, non-union and malunion collectively reported in 3% of the cases [6]. Metatarsal osteotomy union will be defined using cortical continuity [17], with patients failing to show any healing (nonunion) and insufficient cortical continuity (delayed) by the 12-month review, identified in the trial data.

### Participant timeline {13}

The time schedule for participant recruitment, interventions and assessment in this trial will follow the standard clinical pathway embedded within the SOFARI registry (Fig. 3). The recruitment, allocation, surgery and 12 months follow-up time points relevant to the current trial are described in Fig. 1.

### Sample size {14}

The sample size required for the primary outcome was established to provide adequate power to detect half an MCID difference (15.3/2) in the FAOS Pain score between the control flat-cut Weil and experimental wedge-cut groups, with an average estimated baseline standard deviation of 20.8. The MCID and baseline SD were derived from a previous study [15], and 0.5MCID was determined to be a clinically important effect that would influence future clinical decision-making regarding technique selection. A mixed-effects model (analysis of covariance (ANCOVA)) was selected as the most appropriate to answer the question posed, with power (*β*) at 0.9 and *α* of 0.05, with an allowance for a dropout rate of 10%. The required sample size was determined using GPower [18] to be *N* = 80 patients, with patient age at surgery, sex, body mass index, single/multiple procedures and adjunct procedures included as model covariates.

The sample size required for the secondary outcome was established to provide adequate power to detect a 15% reduction in complication incidence from a baseline of 60% incidence. The reduction in incidence was deemed to be the minimal amount of improvement that would influence future decision-making regarding technique selection in this patient population. A one-sided test within a logistic regression model was selected within GPower, with the *R*^2^ for other predictors in the model (patient age at surgery, sex, body mass index, single/multiple procedures and adjunct procedures) set to 0.1. The required sample size was determined to be *N* = 123 procedures.

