#### Data integrity

All data points for the study core dataset will be retrieved electronically, so comparing to original paper records will not be necessary. Data integrity will be defined in the context of this study as completeness, consistency and validity. An error rate of < 3% will be considered acceptable across the total of fields assessed.

Patients who are otherwise lost to follow-up will be included in the analysis under an intention-to-treat framework. Where appropriate, imputation will be used to provide estimates of outcomes for patients lost to follow-up. To mitigate the effects of loss to follow-up on the analysis, the sample size factored in an estimated dropout rate of 10% to ensure adequate power for analyses requiring listwise deletion of missing data.

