#### Primary outcome analysis

The primary outcome of the trial is postoperative pain at 12 months follow-up represented by the pain subscale of the FAOS. A mixed-effects ANCOVA will be used to test for differences between the groups with the following factors and covariates included in the model:Patient ID (random factors)Baseline FAOS pain subscore (covariate)Age at surgery (covariate)Sex (covariate)Multiple proceduresAdjunct procedures

The overall model fit will be assessed with partial eta^2^ and coefficients (*β*) with 95% confidence limits will describe the strength and direction of relationships between factors and the postoperative FAOS-Pain score. Post hoc comparisons with Dunnett tests (against control) will be used to compare osteotomy groups. Cohen’s *d* will be used to report the effect size of differences between the groups. A Cohen’s *d* exceeding 0.36 will be deemed clinically significant.

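### On the protocol's own inputs, 80 patients give about 37% power for half the MCID without covariate gain (47–62% at assumed baseline correlations of 0.5–0.7), not 90%

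*Protocol article*

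**What the plan says.** Sample size {14} in the protocol article sets the primary target as the ability to "detect half an MCID difference (15.3/2) in the FAOS Pain score between the control flat-cut Weil and experimental wedge-cut groups". The SD is a baseline value, taken as 20.8. The section names an ANCOVA-type mixed-effects model in GPower, "with power (*β*) at 0.9 and *α* of 0.05, with an allowance for a dropout rate of 10" per cent, and reports 80 patients. Trial design {8} specifies two parallel groups, allocated 1:1.

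The target appears twice more. Primary outcome measures describes the MCID of 15.3, "with a difference between groups equal to half this (7.7) deemed sufficient to guide future decision-making". Primary outcome analysis states: "A Cohen’s *d* exceeding 0.36 will be deemed clinically significant".

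The section on Data integrity relies on the dropout allowance, saying that "the sample size factored in an estimated dropout rate of 10% to ensure adequate power for analyses requiring listwise deletion of missing data".

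Primary outcome analysis defines the outcome as FAOS pain at 12 months and adjusts for baseline FAOS pain. The covariates listed under Sample size do not include baseline pain, and that section gives no correlation, R² or residual SD for the primary outcome.

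**The concern.** A difference of 7.65 on an SD of 20.8 is a little over a third of a standard deviation. A two-arm trial of 80 patients does not normally have 90% power for an effect of that size, so the printed inputs and the printed answer appear not to belong together.

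This is the primary outcome, and the protocol says that half the MCID is enough to guide the choice of technique. The Principles section of the statistical methods also ties interpretation to the effect sizes in the sample size calculation. If the 90% is wrong, a non-significant result would carry an assurance against a 7.65-point benefit that the design does not provide.

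**Working it through.** **Inputs.** Difference 15.3/2 = 7.65; SD 20.8; alpha 0.05; power 0.90; dropout 10% (all Sample size {14}); two equal groups (Trial design {8}). Sidedness is not stated for the primary outcome; the ANCOVA F test is two-sided.

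**Effect size.** d = 7.65/20.8 = 0.368, which agrees with the 0.36 threshold in Primary outcome analysis. GPower's ANCOVA routine takes Cohen's f; for two equal groups f = d/2 = 0.184.

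**Method.** Noncentral F with numerator df 1, denominator df N − 2 − q (q covariates) and noncentrality λ = N·f².

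**Reproducing the protocol's 80.** With f = 0.368, λ at N = 80 is 80 × 0.1353 = 10.8, and power is 0.901. The smallest N reaching 0.90 is exactly 80 for each covariate count tried (0, 1, 5 and 6). No dropout is included; adding 10% gives 80/0.9 = 89.

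**The same calculation with f = 0.184.**
- N for 90% power: 313 (λ = 313 × 0.0338 = 10.6). With 10% dropout, 313/0.9 gives 348.
- Normal-approximation check: 2 × (1.960 + 1.282)² / 0.368² gives 156 per arm, 312 in total.
- Power at N = 80: λ = 80 × 0.0338 = 2.7, power 0.368 (normal approximation 0.376).
- Power at 72 analysed (80 × 0.9): 0.337.
- Variants on the normal approximation: a one-sided test needs 254, and 80% power needs 234. One-sided power at N = 80 is 49%. None of these gives 80.

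**Baseline adjustment.** If baseline and 12-month pain correlate at r, f becomes 0.184/√(1 − r²), and the detectable difference shrinks by √(1 − r²). The values of r are assumptions.

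| Assumed r | Power for 7.65 at N = 80 | at N = 72 | Analysed N for 90% | Difference detectable at 90%, N = 80 |
|---|---|---|---|---|
| 0 | 37% | 34% | 313 | 15.3 |
| 0.5 | 47% | 43% | 236 | 15.28 × 0.866 = 13.2 |
| 0.7 | 62% | 58% | 161 | 15.28 × 0.714 = 10.9 |
| 0.8 | 77% | 73% | 114 | 15.28 × 0.600 = 9.2 |

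Power of 90% for 7.65 points needs r of about 0.87 at N = 80, or 0.88 at N = 72. For 15.3 points without covariate gain, power is 90% at N = 80 and 87% at N = 72.

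**The case against.** Four objections deserve an answer. They limit what can be said about the cause, the dropout allowance and the exact power, but they do not rescue the 90%.

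*The cause is not shown.* A reader might conclude that d was demonstrably entered as f. The protocol prints no f and no GPower menu choice, and other routes also return 80: the full 15.3 points in a two-group ANCOVA, a one-sample or paired calculation with an effect of 0.368, or a two-group, two-time-point interaction with f = 0.184 and correlation 0.5. None of these is a valid calculation for a 7.65-point between-group difference at 12 months. The shortfall is the same whichever was used.

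*The dropout allowance might be in the figure.* A reader might infer that 80 is certainly un-inflated. That depends on the same inference: 72/0.9 is also exactly 80. What can be said is that 80 matches the un-inflated ANCOVA output and that the allowance cannot be verified from the protocol.

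*Eighty may be the number analysed.* Plans for assessment and collection of outcomes {18a} continues data collection until the minimum sample size is reached with complete records, and {18b} refills the slots of participants removed because the intervention protocol was not followed. On that reading the 72-patient figures do not arise. The dropout language under Sample size and Data integrity points the other way, so the protocol leaves this unsettled.

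*The model does better than an unadjusted comparison.* This stands in part. The 37% figure, and any statement that the trial can reliably detect only the full MCID, are the zero-correlation case, whereas the planned model adjusts for baseline pain. Power is then higher, but r of 0.87 is a demanding requirement and the protocol does not claim it. Averaging the 3-, 6- and 12-month scores would help more: under compound symmetry with r = 0.8, power would be about 93% at 80 and 90% at 72. However, at r = 0.5 it would be only 71% at 80, and Primary outcome analysis fixes the outcome at 12 months.

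It would also go too far to say that a null result will be misread. Coefficients with 95% confidence limits are planned, so the imprecision will be visible.

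**Conclusion.** The stated 90% power for half the MCID is wrong on the protocol's own inputs. Those inputs need 313 analysed patients, about four times 80 (313/80 = 3.9). Power at 80 analysed is about 37% without covariate gain and 47–62% for r between 0.5 and 0.7.

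The conclusion rests on the printed difference, SD, alpha and two-group design, a two-sided test, the baseline SD of 20.8 also holding at 12 months, and the outcome being the 12-month score. The range above 37% rests on assumed correlations. The d-for-f explanation is the likeliest one, but the verdict does not depend on it. Because this concerns the primary outcome and the remedy is only wording, it should be corrected.

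**What to change.** Keep 80 patients and restate the power in Sample size {14}, for example:

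> With 80 patients analysed, the trial has 90% power for a difference of about 15.3 points without covariate gain (about 13.2 points if the baseline correlation is 0.5, 10.9 if it is 0.7). Power for 7.65 points is about 37%, or 47–62% for correlations of 0.5–0.7.

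Then:
- State whether 80 means enrolled patients or complete records, and reconcile Sample size and Data integrity with {18a}. If 80 are enrolled and 10% are lost, give the figures for 72 analysed: 34% (43–58%) for 7.65 points, and 87% for 15.3 points without covariate gain.
- Remove the statements under Sample size and Data integrity that a 10% allowance secures adequate power, or show how it was derived.
- Keep half the MCID and d above 0.36 as the thresholds of relevance. Add that a non-significant result cannot by itself exclude a 7.65-point benefit and must be read from the confidence interval.

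The cost is a wording amendment to the protocol and the registry record, and a less favourable stated power. No extra patients are needed. Enlarging the trial instead would be a major change: Recruitment {15} reports 87 patients treated by the principal investigator in 12 months, so 348 would be four years of that surgeon's volume even if every patient enrolled (348/87 = 4). The other participating surgeons' volumes are not given.
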